**Fig. 3 Fig3:**
[figure not shown]
A priori power analysis estimation based on effect sizes of 0.02 (top), 0.05 (centre) and 0.10 (bottom) for a confidence interval of 95% and a sample size per group of 0 to 1000. Calculations were done using the pwr 1.3–0 package in R [140]

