#### Assessment (refugees)

Data collection from refugees begins with a face-to-face interview conducted by one of the NAT counsellors (see Sect. Intervention description) and continues with 10-minute monthly online assessments (Well-being Monitor). Approximately 6 to 9 months after the initial screening, refugees will be invited to a face-to-face follow-up interview.

At the start of the face-to-face baseline interview, we will ask for demographic information, screen for trauma related symptoms, and collect information on social and economic integration. The follow-up interview after 6–9 months will re-assess levels of psychological distress and integration.

The 15-item Refugee Health Screener [123] will be used to assess the severity of trauma related reactions. The RHS was adapted from validated instruments for depression, anxiety and PTSD to screen for trauma related reactions in refugee populations. Each item is rated on a scale from 0 (not applicable at all) to 4 (extremely) and a total score of items 1–13 indicates the severity of symptoms (0–52) and the intensity of treatment required. Items ask for instance for nightmares, loss of interest or other trauma related symptoms. Items 14 and 15 are taken into account in a qualitative way. The RHS was recently validated with refugees in the German context [124]. Kaltenbach et al. [124] found high sensitivity and good feasibility, reliability and validity for both the self-rating and interview versions. Strong psychometric properties of the RHS were also found in other studies in Germany [147, 148] and elsewhere [149, 150].

An adapted version of the Appetitive Aggression Scale [139] for refugees will be used to assess aggression. The AAS is a 15 item semi structured interview that measures appetitive aggression according to the extent of agreement to statements, on a scale ranging from 0 (disagree) to 4 (agree) for each item. A total sum score will be used to measure severity of aggression (max 60).

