[3] To assess the effectiveness of NAT compared to the comparison groups (see Tables 1 and 4), we will combine the figures resulting from RDD with traditional approaches (GLM, clinical significance). In the RDD, we will calculate a local average treatment effect (LATE) of the intervention on primary (RHS-15) and secondary (LSNS, BRS, SWLS, SSS8) outcomes (see Table 1). To this end, we will firstly test whether the main criteria for a valid RDD are held. Using a graphical method (scatterplot), we will examine the relationship between the eligibility (RHS at baseline) and outcome (follow-up) variables. We expect the RHS score to be discontinuous at the cutoff values. In contrast, we do not expect to see discontinuities in relevant covariates at the cutoff, which would violate the assumptions of an RDD. Next, separate regression lines will be fit on both sides of a cutoff value using an ordinary least squares (OLS) regression as the starting point. Alternative functional forms will be tested with the goal of ensuring an unbiased estimation. The LATE will be computed directly as the difference between the regression lines at the cut-off (intercept). To test the statistical significance of the difference between the two conditions, we will use a *t*-statistic, dividing the treatment effect (difference between regression lines at cut-off) by the sum of the square of the standard errors of the comparison group (*SE*_*comparison*_) and the intervention group (*SE*_*interventio*n_). The calculated *t*-statistic will then be compared to a critical value from the *t*-distribution for the given degrees of freedom (*DF*). The degrees of freedom will be determined based on the number of the observations and the parameters estimated in the two separate regressions. In the most simple form, *DF = n*_*comparison*_
*+ n*_*intervention*_
*- 4*. The test will be two-sided. Moreover, we will run falsification tests and sensitivity analysis to ascertain the validity of the RDD [178], examine whether results are sensitive to the choice of bandwidth [144], run placebo tests on exogenous covariates and on the outcome at values other than the actual cutoffs [145]. Prespecified subgroup analyses will explore potential heterogeneity in treatment effects across different demographic and clinical characteristics. Adjusted analyses will account for potential confounding factors identified a priori.

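### The regression-discontinuity t-statistic divides the jump by its variance instead of its standard error: a square root is missing

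*Protocol article*

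**What the plan says.** The rule is in the protocol article under Statistical methods for primary and secondary outcomes, item [3], where the text prescribes each step of the test:

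- **Fit:** "separate regression lines will be fit on both sides of a cutoff value using an ordinary least squares (OLS) regression as the starting point".
- **Effect:** "The LATE will be computed directly as the difference between the regression lines at the cut-off (intercept").
- **Test statistic:** "dividing the treatment effect (difference between regression lines at cut-off) by the sum of the square of the standard errors of the comparison group" and of the intervention group.
- **Reference distribution:** a t critical value. "The degrees of freedom will be determined based on the number of the observations and the parameters estimated in the two separate regressions"; in the simplest case this is n_comparison + n_intervention − 4.
- **Sidedness:** "The test will be two-sided".
- **Outcomes:** "primary (RHS-15) and secondary (LSNS, BRS, SWLS, SSS8) outcomes".

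No square root is mentioned in this section or elsewhere in the article.

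**The concern.** The two lines are fitted to different people, so the two intercepts are independent and their variances add. The sum of the squared standard errors is therefore the variance of the jump. A t-statistic needs the square root of that sum. Dividing by the variance leaves a quantity in units of one over the outcome, and comparing it with a t critical value has no justification.

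This is the only significance test that the article gives for the discontinuity effect, and it covers outcomes on quite different scales. Followed literally, it would hide real effects on a scale with a wide numerical range and declare spurious ones on a scale with a narrow range. Rescoring the same data from a sum to a mean could reverse the conclusion.

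**Working it through.** The article has no p-value or power figure for this test to reproduce, so the check is algebra followed by illustration.

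**Inputs from the article**
- Formula, fit, degrees of freedom and sidedness: as set out above.
- Significance level: none is stated with the test. I take 0.05 because the power figure (Fig. 3) is drawn "for a confidence interval of 95" per cent.
- Primary scale: "a total score of items 1–13 indicates the severity of symptoms (0–52"), under Assessment (refugees).

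**Assumed, because the article does not give them:** residual SD, number per side and bandwidth. The Limitations section says that group numbers cannot be predicted accurately.

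**Algebra (no assumed figure needed)**
- V = SE_c² + SE_i² is the variance of the jump, and s = √V is its standard error.
- Correct statistic: t = jump / s, with n_c + n_i − 4 degrees of freedom.
- Statistic as written: jump / V = (correct t) / s.
- Two-sided type I error as written: 2·P(T > t_crit × s). This equals 0.05 only when s = 1.

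**Type I error as written, 100 per side (196 df)**

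| SE of jump, s | Type I error |
|---|---|
| 0.25 | 0.62 |
| 0.5 | 0.33 |
| 1 | 0.05 |
| 1.5 | 0.0035 |
| 2 | 0.0001 |

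**RHS sum score, assuming SD 8 and 80 per side.** With baseline scores spread evenly over the bandwidth, the SE of an intercept at the boundary is 2σ/√n. The normal approximation is used.
- Each SE = 2 × 8 / √80 = 1.79. V = 6.40 and s = 2.53.
- Jump needed for significance: correct 1.96 × 2.53 = 5.0 points; as written 1.96 × 6.40 = 12.5 points.
- Type I error as written: 2·P(Z > 1.96 × 2.53) ≈ 7 × 10⁻⁷.
- A jump of 2.8s has 80% power with the correct test. As written, the power is P(Z > 1.96 × 2.53 − 2.8) ≈ 0.015.

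**Range with the same SE formula**
- SD 10, 50 per side: s = 4.0, type I error about 5 × 10⁻¹⁵, and the 80% power becomes about 0%.
- SD 8, 200 per side: s = 1.6, and the 80% power becomes about 37%.
- SD 6, 200 per side: s = 1.2, type I error about 0.019, and the 80% power becomes about 67%.

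**Dependence on units.** Take an assumed jump of −4 RHS points with SEs of 1.2 and 1.3 and 100 per side, so V = 1.44 + 1.69 = 3.13.
- Sum score: correct t = −4/√3.13 = −2.26, p = 0.025. As written t = −4/3.13 = −1.28, p = 0.20.
- Same data divided by 13 (item mean, 0–4): correct t and p are unchanged. As written V = 3.13/169 = 0.0185 and t = −16.6, p about 3 × 10⁻³⁹.

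**Simulation:** two OLS lines, bandwidth 6 points, SD 6 to 10, 50 to 200 per side, 2,000 runs per setting.
- Correct formula: null rejection 3.7% to 5.6% in every setting, on the sum and on the item mean.
- As written, RHS sum: null rejection 0.0% to 2.0%.
- As written, RHS item mean: null rejection 51% to 85%.
- SD 8, 100 per side, true jump of 5 points on the sum score: 59% rejection with the correct formula, 2% as written.

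**The case against.** The strongest reply is that this is a slip of wording. The rest of the recipe (two OLS fits, intercept difference, degrees of freedom, two-sided t) is the ordinary test, and regression software would report the usual standard error. The invalid p-values would arise only if someone coded the sentence by hand. That is plausible, but the article spells the formula out, so the text still needs correcting for anyone who implements or replicates it.

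Several limits also stand:
- The two formulas agree if the summed variances happen to equal 1, or if the jump is exactly 0. Near 1 the distortion is modest: with the normal approximation, s = 1.1 gives a type I error of 0.031 and s = 0.9 gives 0.078.
- The size of the error for the RHS depends on SD and numbers that the article does not state, so it can only be given as a range.
- The liberal direction needs a scale with a narrow range. The article states sum or total scores for the RHS, SWLS and SSS8 and no scoring rule for the six-item BRS. With an assumed item-level SD of 0.7 and 80 per side, a BRS item mean gives s = 0.221 and a type I error of about 66%; a BRS sum gives s = 6 × 0.221 = 1.33 and about 0.9%.
- The mixed-model likelihood-ratio tests and the chi-squared tests are unaffected. The mixed models are additional and conditional on being robust, so they do not replace this test.

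**Conclusion.** The formula is wrong as written. It divides by the variance of the jump, so the statistic depends on the units of measurement and does not follow the stated t-distribution. That conclusion rests on algebra alone.

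Its practical size rests on assumptions. For the RHS sum score, over the ranges examined, the test would be too conservative, from moderately (67% power where 80% was expected) to completely. For any outcome scored so that the standard error of the jump falls well below 1, it would be badly anti-conservative. The problem is confined to the regression discontinuity tests of the primary and secondary outcomes. The stated degrees of freedom are right for two straight lines fitted separately.

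**What to change.** In item [3] of the statistical methods, define the statistic as t = jump / √(SE_comparison² + SE_intervention²) and leave the reference distribution as it is. This corrects the stated error completely.

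An optional alternative is to take the jump and a robust standard error from one regression with a side-of-cut-off indicator, the baseline RHS centred at the cut-off, and their interaction. That is a preference and the correction does not depend on it.

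The cost is one sentence. Design, data collection and sample size do not change.

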All steps of the NAT counselling intervention are carried out by trained counsellors under the supervision of NET experts (from vivo international e.V. and the University of Konstanz) or otherwise trained licensed psychotherapists. The NAT counsellors themselves are peers in terms of their cultural and migrant background and therefore have similar biographical experiences, moreover are familiar with and well-integrated into German culture and have good language skills (mother tongue and German) and strong social skills. It is recognised that conditions in the countries of origin vary and therefore the requirements for recruitment and inclusion of counsellors in the project programme have not been rigidly defined but are rather based on the real-world setting. However, high motivation, impartiality and strong integrative and social skills are prerequisites for participation in the NAT training programme. Exclusion criteria for counsellors include: suffering from a mental illness, holding extreme or radical religious or ideological views, have insufficient language skills or illiteracy in German. In addition, we provide a screening for PTSD symptoms in an initial session using the PTSD Checklist for DSM-5 [127, 128]. Following this assessment, participants are provided with an individualised information session on the potential psychological impact of the project and supported to make their own decision as to whether or not they are ready to train and work as a counsellor and to undergo counselling themselves. Due to the sensitive nature of this personal health information, no written records are made or kept.

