### Outcomes

Outcomes of interest include the participants´ somatic and psychological symptoms, social integration, mental health literacy of the client, general life satisfaction, and post-migration stressors. Baseline and a follow-up assessment will be administered by NAT counsellors in face-to-face interviews and will assess psychological symptoms and social integration. Additional instruments are listed in Table 3 will be administered online.

**Table 3 Tab3:** List of instruments of the well-being monitor

Outcome	Measure	Author	Admin.
Somatic symptoms	Somatic Symptom Scale-8 (SSS8)	Gierk et al. [129]	online
Psychological symptoms	Refugee Health Screener (RHS-15)	Hollifield et al. [130]	both
Life satisfaction	Satisfaction with Life Scale (SWLS)	Diener et al. [131]	online
Social networks	Lubben Social Network Scale (LSNS-6)	Lubben [132]	online
Social and economic integration	Immigration Policy Lab Integration Index (IPL-12)	Harder et al. [133]	both
Mental Health literacy Scale	Mental Health Literacy Scale (MHLS)	O’Connor et al. [134]	online
Resilience	Brief Resilience Scale (BRS)	Smith et al. [135]	online
Self-efficacy	General Self-Efficacy Short Scale-3 (GSE-3)	Doll et al. [136]	online
Food insecurity	Food Insecurity Experience Scale (FIES)	Cafiero et al. [137]	online
Food environment	Access to preferred food types	Adapted from Hadley et al. [138]	online
Aggression	Adapted version of the event scale of the appetitive aggression scale	Weierstall et al. [139]	both
Note: Both = to face-to-face interviews and online			

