	The number of participants with subclinical symptom levels at baseline who do not require treatment after 6–9 months is higher in participants who received NAT than in the control group.	The number of participants with subclinical symptom levels at baseline who do not require treatment after 6–9 months is equal in participants who receive the adapted NET compared to the control group.	2b
Is NAT **effective** (symptom reduction)?	Symptom reduction in participants with subclinical symptom levels is stronger in participants receiving NAT than in the control group (see Table 1).	Symptom reduction in participants with subclinical symptom levels is the same in participants receiving NAT compared to the control group (see Table 1).	3
[4] Is the programme generally cost-**effective**?	The financial costs of the NAT counselling intervention are lower than those of other interventions.	The financial cost of the NAT counselling intervention is equal to or higher than other interventions.	4

[2a+b] Chi-squared tests will be used to compare the frequency of participants with subclinical symptom levels requiring more/less intensive treatment during the programme. Logistic regression analysis will be considered to estimate the odds of refugees with or without NAT requiring more/less intensive treatment (Table 4).

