Generalised linear mixed models (GLMM) with subgroups defined by the RDD will be used in addition and allow for integration of multiple follow-ups, if robust (*N*_min_ is sufficient to detect a small to moderate effect). Thus, to test the efficacy of NAT in comparison to our controls in regards to primary and secondary outcomes, we plan to use separate generalised linear mixed models (GLMMs) in R. To account for non-independence of measurements, we will include individuals as a random part of the models. To account for repeated measures, we will control the within-group variance for the effect of time, i.e. baseline and 3 and 6-month follow-ups, according to A Field, Z Field and J Miles [179]. To estimate the significance of the fixed terms, we plan to fit the models using maximum likelihood (ML), and compare models with and without each fixed term using likelihood-ratio tests [180]. In cases where the interaction term is significant, we will use post hoc Tukey tests using the R package emmeans [181] to assess which contrasts differ significantly. To correct for multiple comparisons controlling the false discovery rate, we will further adjust P-values accordingly [182].

Additionally, effect sizes will be estimated by calculating Cohen’s d [183] for within and between group differences following W Lenhard and A Lenhard [184]. Clinically significant change will be calculated using the reliable change index, following NS Jacobson, LJ Roberts, SB Berns and JB McGlinchey [185].

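### The named effectiveness analyses treat clients as independent although each peer counsellor delivers NAT to several of them, so the NAT-side variance is understated if outcomes vary by counsellor

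*Protocol article*

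**What the plan says.** On delivery, the Eligibility criteria section states: "All steps of the NAT counselling intervention are carried out by trained counsellors under the supervision of NET experts" (or other trained licensed psychotherapists). It adds that requirements for counsellors were not rigidly defined. Counsellors also collect data. Under Assessment (refugees): "Data collection from refugees begins with a face-to-face interview conducted by one of the NAT counsellors". Under Outcomes: "Baseline and a follow-up assessment will be administered by NAT counsellors in face-to-face interviews". Most instruments, including the RHS-15, are also or only collected online.

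On analysis, the section Statistical methods for primary and secondary outcomes names three approaches to effectiveness:

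- Hypotheses 2a and 2b: "Chi-squared tests will be used to compare the frequency of participants with subclinical symptom levels", with logistic regression to be considered.
- Hypothesis 3, regression discontinuity: "separate regression lines will be fit on both sides of a cutoff value using an ordinary least squares (OLS) regression". On the reference distribution: "The degrees of freedom will be determined based on the number of the observations and the parameters estimated in the two separate regressions", in the simplest form the two group sizes added together minus 4. The test is two-sided.
- Hypothesis 3, mixed models: "To account for non-independence of measurements, we will include individuals as a random part of the models".

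The article names no counsellor or site term, clustered standard error, intraclass correlation or design effect.

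**The concern.** A random effect for the individual absorbs the correlation between one person's assessments. It does nothing for the correlation between two people treated by the same counsellor. Counsellors with varied backgrounds and skill may well differ in the results they obtain, and clients matched to a counsellor by culture may resemble each other for other reasons too. If so, clients of one counsellor carry partly overlapping information about the NAT effect, and an analysis that counts each client as a full independent observation overstates its precision.

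At stake is the error rate of every named effectiveness test. The error runs towards intervals that are too narrow and towards declaring NAT effective too often. The article addresses dependence explicitly and fixes both the random part and the rule for degrees of freedom, so this is a matter of what is written and not only of detail left for later.

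**Working it through.** **Inputs from the document.** NAT is delivered by counsellors; the only random part named is the individual; degrees of freedom come from the number of observations; the test is two-sided. The 95% confidence level in the power figure caption corresponds to 5%. The text states no design effect or powered sample size, so there is no figure of the plan to reproduce.

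**Inputs that are assumed.** Clients per delivering counsellor, m = 8 to 20; intraclass correlation on the NAT side, ICC = 0.02 to 0.10; arms of equal size; no clustering among controls.

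**Formulas.**

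- NAT-side design effect: DE = 1 + (m − 1) × ICC.
- Variance of the NAT-minus-control contrast, relative to that assumed: V = (1 + DE)/2.
- Real two-sided error of a nominal 5% test: 2 × (1 − Φ(1.96/√V)).
- Effective clients per counsellor: m/DE.

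**Results.**

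| m | ICC | DE | V | 1.96/√V | Real error | Effective clients |
|---|---|---|---|---|---|---|
| 8 | 0.02 | 1.14 | 1.07 | 1.895 | 5.8% | 7.0 of 8 |
| 8 | 0.10 | 1.70 | 1.35 | 1.687 | 9.2% | 4.7 of 8 |
| 20 | 0.02 | 1.38 | 1.19 | 1.797 | 7.2% | 14.5 of 20 |
| 20 | 0.10 | 2.90 | 1.95 | 1.404 | 16.0% | 6.9 of 20 |

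With m = 5 and ICC 0.01 to 0.02, V is 1.02 to 1.04 and the real error is 5.2% to 5.5%.

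**Check by simulation.** A t-test that ignores counsellors was applied with no true NAT effect, 4,000 runs per setting, with 10 or 20 counsellors and 5 to 20 clients per counsellor in each arm.

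- No counsellor effect: error 4.4% to 4.8%.
- NAT-only counsellor effect, ICC 0.05: 6.2% to 10.4%.
- NAT-only counsellor effect, ICC 0.10: 7.9% to 15.5%.
- Only an interviewer effect shared by both arms, ICC 0.05 to 0.10: 3.7% to 4.7%.
- Delivery ICC 0.05 plus shared interviewer ICC 0.05 to 0.10: 4.9% to 9.9%, above 5% in 7 of 8 settings.

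The inflation therefore comes from delivery. An interviewer effect common to both arms largely cancels in the contrast and by itself makes the naive test slightly conservative.

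**The case against.** **The article leaves model detail open.** Ordinary least squares is called a starting point, the degrees of freedom are given in their simplest form, adjusted analyses are promised for confounders, and an analysis plan that is not shown may say more. This stands in part: the wording does not exclude a counsellor term. But where dependence is discussed, only the individual is named, and adjustment for confounders is not offered as a correction for clustering.

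**The size is unknown and may be negligible.** This stands. Number of counsellors, caseload and correlation are all absent. The regression discontinuity estimate uses only clients near a cutoff, so the relevant m there is smaller than the full caseload.

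**A reader might infer that counsellors' interviewing adds to the inflation, with both arms clustered alike.** The document does not support this. It describes one pool of NAT counsellors who interview clients and does not split them by arm, so the interviewer effect is crossed with arm. It would add to the problem only if interviewers differed between arms. Self-completed online outcomes have no interviewer effect, and nothing says the delivering counsellor takes that client's own follow-up. Clustering of psychotherapy controls by therapist could act in the same direction as delivery clustering, but the article gives no basis for sizing it.

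**A reader might also infer that the effective NAT sample is nearer the number of counsellors than the number of clients.** In three of the four corner cases in the table it is nearer the number of clients. Only m = 20 with ICC 0.10 fits that description.

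**Conclusion.** The point holds for clustering by the counsellor who delivers NAT. As written, all the named effectiveness analyses take clients as independent, and the variance on the NAT side is understated whenever outcomes differ between delivering counsellors. Under the assumed ranges for m and ICC, with equal arms and unclustered controls, the standard error is too small by a factor of 1.03 to 1.40 (the square roots of 1.07 and 1.95), and the real two-sided error is about 6% to 16% in place of 5%. It falls close to 5% when each counsellor contributes only a few clients. The direction is firm if counsellors differ in effect. The size cannot be fixed from the document. The plan should be amended, but the point does not undermine the design.

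**What to change.** 1. **Mixed model.** Add a partially nested counsellor effect for NAT delivery: a random NAT slope by delivering counsellor, with controls unclustered or clustered by their own provider where known. The cluster must be the person who delivers NAT, because controls have no NAT deliverer. Add the interviewer as a crossed random effect for face-to-face outcomes, and site as a fixed effect.
2. **Regression discontinuity and hypotheses 2a and 2b.** Use standard errors clustered by delivering counsellor, with a small-sample correction. For 2a and 2b, make a logistic model with these standard errors the main analysis in place of the chi-squared test.
3. **Data.** Record the delivering and the interviewing counsellor for each client. The adherence protocol completed after each NAT session should help for NAT clients, but it does not cover controls, and the article does not say that screening records store who conducted the interview.
4. **Assumptions.** State the expected number of counsellors, clients per counsellor and intraclass correlation.

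The cost is analysis wording and one or two identifier fields. Intervals become somewhat wider, and the small-sample correction matters more if few counsellors are active.

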## Trial design

The present study employs a naturalistic parallel groups design, integrating a regression discontinuity statistical approach for quasi-randomisation with a classical longitudinal design. The resulting pattern of evidence will indicate the sustainability, cost-effectiveness and effectiveness of the programme while we ensure that all study participants receive evidence-based treatment.

Assessments include an in-person baseline screening, monthly online or assisted self-assessments (hereafter: well-being monitor), and an in-person follow-up at 6–9 months post-baseline. Given the central role of the peer counsellors in the programme, we will assess their training and supervision in terms of acceptability, efficiency and motivations, through focus group discussions and survey-based evaluations. These evaluations will take place before the counsellors begin their active work and after they have completed a substantial number of NAT steps (screenings, referrals, checklist intakes, lifeline sessions and narrative event-telling sessions).

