## Interventions

### Explanation for the choice of comparators

In this naturalistic study, the following potential comparators to NAT (treatment condition) evolve: (1) NAT clients awaiting treatment; (2) clients with clinically relevant symptoms who are either (2a) waiting for psychotherapy or (2b) receiving psychotherapy; (3) clients without symptoms waiting for follow-up; and (4) clients before vs. after NAT (individual trajectories of symptom development, Table 1).

**Table 1 Tab1:** Constellation of comparators

Treatment condition	Control condition	Limitation	Mitigation
[1] NAT	Awaiting NAT (RHS 13–36)	Reduced follow-up time points for those who wait for treatment; unknown N	-
[2] NAT	[2a] PT waiting [2b] PT receiving	Clients might still wait but may have started, or already finished PT; higher symptoms of the control group at baseline	Statistical control for the number of treatment sessions, use of the RDD
[3] NAT	Watchful waiting (RHS < 13)	Lower symptoms of the control group at baseline, low symptom levels generally	Evaluate number of clients who present with improving vs. deteriorating symptoms rather than
[4] After NAT	Before NAT	Within subject comparison; potential confounding factors	-

Note: RHS-15 = 15 item Refugee Health Screener with a sum score indicating symptom severity; PT = Psychotherapeutic sessions provided by a licensed Psychotherapist. Threshold to clinical relevance is suggested for ≥37. Watchful waiting is indicated for clients with ≤12 points

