### Recruitment

Social workers on site inform refugees in collaborating initial intake facilities and hand out flyers about the programme, including participation instructions. Additionally, NAT counsellors will be present in the facilities on a regular basis. With it, refugees who would like to participate can request to register for participation. Moreover, with bi-monthly visits at the initial intake facilities, public health experts and research assistants will invite refugees to participate in the online self-assessments of the Well-being Monitor.

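### The mixed model puts interview and online RHS scores on one time axis and does not say which record supplies the 6-month point, so a mode difference can pass for within-person change

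*Protocol article*

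**What the plan says.** On how the RHS is collected, the Protocol article is consistent:

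- **Baseline.** Assessment (refugees): "Data collection from refugees begins with a face-to-face interview conducted by one of the NAT counsellors".
- **Monthly.** The same section says data collection "continues with 10-minute monthly online assessments (Well-being Monitor"). Trial design adds that these may be assisted: "monthly online or assisted self-assessments (hereafter: well-being monitor), and an in-person follow-up at 6–9 months post-baseline".
- **Later visit.** Outcomes: "Baseline and a follow-up assessment will be administered by NAT counsellors in face-to-face interviews". The later interview is thus in the same mode as baseline.
- **Table 3.** The RHS-15 is coded for both modes, with the note "Both = to face-to-face interviews and online". The IPL-12 and the aggression scale carry the same code. The secondary outcomes named for the regression discontinuity analysis (LSNS, BRS, SWLS, SSS8) are online only.

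On analysis, the mixed-model paragraph under Statistical methods for primary and secondary outcomes says "we will control the within-group variance for the effect of time, i.e. baseline and 3 and 6-month follow-ups". Individuals form the random part. The fixed terms are not listed. Within-group and between-group Cohen's d and a reliable change index follow, without naming the records they use. Table 1, row [4], gives the limitation of the before/after comparison as "Within subject comparison; potential confounding factors" and leaves its mitigation cell blank (a dash).

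**The concern.** An interviewer-administered score and a self-completed score on the same scale need not sit at the same level, especially for symptoms that carry stigma. Assessment (refugees) reports that both RHS versions are valid. It does not say that they give the same mean score. If the levels differ, a person whose symptoms have not changed appears to change when the mode changes. The within-person results have no concurrent control to absorb this: comparator [4], within-group Cohen's d, and reliable change. At stake is whether an apparent improvement after Narrative Trauma Work (NAT) partly reflects how the question was asked.

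**Working it through.** The plan states no figure on this point, so there is none to reproduce.

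**Step 1: mode by time point in the mixed model**

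| Time point | Possible RHS source |
|---|---|
| Baseline | Counsellor interview only |
| 3 months | Online or assisted monitor only (no interview is planned then) |
| 6 months | Monitor, or the 6 to 9 month interview; not specified |

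Between baseline and 3 months, mode and time are collinear. No covariate added later can separate them from those two points alone.

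**Step 2: expected bias.** Let s be the online-minus-interview shift and p the online share at a time point.

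- Spurious within-group change from baseline = s × p. At 3 months p = 1, so the change equals s.
- Spurious between-group difference in change = s × (p in NAT − p in control), if s is the same in both groups.

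**Step 3: simulation.** Assumptions, none from the documents: 150 people per group, 150 replicates, between-person SD 6, residual SD 5, no true change, no NAT effect, online scores lower, and half of the 6-month records online unless stated. The model is group × time without a mode term.

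| Scenario | Time, 3 mo | Time, 6 mo | Group × time, 3 mo | Group × time, 6 mo |
|---|---|---|---|---|
| s = −1, both groups | −0.96 | −0.56 | −0.06 | 0.11 |
| s = −2, both groups | −1.97 | −0.99 | −0.09 | −0.09 |
| s = −4, both groups | −4.01 | −2.01 | 0.04 | 0.05 |
| s = −2; online at 6 months: 20% NAT, 80% control | −2.05 | −1.58 | 0.03 | 1.15 |
| s = −2 in control, −3 in NAT | −1.99 | −0.98 | −1.02 | −0.52 |

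Monte Carlo error for a 3-month time effect is about √(2 × 25/150)/√150 = 0.05, and for group × time about √2 times that, 0.07. The group × time values in the first three rows are therefore compatible with zero. In the fourth row the formula gives −2 × (0.2 − 0.8) = +1.2, against 1.15 simulated.

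**Step 4: what a shift could look like in a before/after comparison.** Assume an SD of change of 8 and 100 clients, with an interview score before and an online score after. Then d = s/8 and t = d × √100:

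- 1 point: d = 0.125, t = 1.25
- 2 points: d = 0.25, t = 2.5
- 4 points: d = 0.5, t = 5.0

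Under these assumptions the 2-point case would already be significant at the two-sided 5% level with no true change.

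**Step 5: does a mode term cure it?** With an additive mode term and a common shift, the spurious time effects fall to within 0.13 points of zero. This works only because the assumed 6-month data contain both modes. If the shift differs by group by 1 point, group × time stays at −1.02 (3 months) and −0.50 (6 months). These fits are ordinary least squares. That matches a random-intercept fit for the balanced model without the mode term and approximates it once the term is added.

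**The case against.** The strongest reply has five parts.

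- **The article does not exclude a mode term.** A reader might infer that it does. The fixed terms are simply not listed, and adjustment for confounders chosen in advance is promised in general terms. A covariate list may sit in an analysis plan that is not shown. This stands, and a missing mode term is not the point here. What remains is that three stated time points mix modes and the 6-month record is not named.
- **The exposed model is supplementary.** The mixed model is added to the regression discontinuity analysis and is conditional on sufficient numbers. Hypotheses 2a and 2b are set at 6 to 9 months, where an interview is available at both ends. This also stands and limits the reach of the point. However, nothing in the statistical section requires same-mode records.
- **Hypothesis 3 is a between-group contrast.** A reader might infer that the NAT effect itself is biased. The documents do not show this: a common shift cancels, and everyone is invited to both the monitor and the follow-up interview. An unequal mode mix is plausible, since Table 1 concedes that waiting clients have fewer follow-up points and the interviewers are unblinded NAT counsellors. That is inference, not something the article states.
- **Comparator [4] can be same-mode.** Clients may have online scores before and after NAT, or interviews at both ends. True, so the bias arises only where an online score is set against the interview baseline.
- **Loss of assistance is not documented.** A reader might infer that assisted completion ends when clients leave the intake facility, because Recruitment says that "with bi-monthly visits at the initial intake facilities, public health experts and research assistants will invite refugees". That sentence concerns invitations, and no section says that support stops after the move.

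**Conclusion.** The point holds in limited form. The documents establish that the RHS mode differs between baseline and 3 months, and that the source of the 6-month score is open. They do not establish that the two modes score differently or by how much; the 1 to 4 points used above are an assumed range. If a shift exists, it passes in full into the 3-month time effect and in proportion to the online share at 6 months. It also passes into comparator [4], within-group Cohen's d and reliable change where these compare online with interview scores. Bias in the group × time contrast needs a mode mix or a mode effect that differs by group, and neither is stated. This is a worthwhile, inexpensive improvement to a supplementary analysis and to the within-person summaries. It does not invalidate the main design.

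**What to change.** In the mixed-model paragraph of Statistical methods for primary and secondary outcomes:

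1. State that within-person RHS change, within-group Cohen's d, reliable change and comparator [4] use same-mode records: interview at baseline to interview at 6 to 9 months. Analyse online scores as a separate online-to-online trajectory.
2. Name the record (monitor or interview) that supplies the 6-month point in the mixed model.
3. Record mode and assistance (interview, assisted online, unassisted online) at every assessment. Unrecorded assistance may not be recoverable later.
4. Add mode as a time-varying fixed effect in a sensitivity analysis only. It can be identified only around 6 to 9 months, it may absorb selection into attending the interview, and it does not remove a mode effect that differs by group.

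The cost is one extra data field and a few sentences, fewer usable records for the same-mode change score, and wider intervals for the time effect in the sensitivity analysis.
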